##### Biological sample collection

The following bio-specimen will be collected in this study:

Whole venous blood (15 mL).Twenty-four-hour urine sample.Spot urine sample.Saliva.Capillary blood.

All samples will be used only for the purpose of the study. The venous blood will first be centrifuged, separated into aliquots and then stored at −20°C at the KK Segamat and then transported to Monash University Sunway campus for storage. Other samples will be stored at −20°C storage. The freezer room for the stored samples will be under lock and key with restricted access.

##### Blood sampling

Whole blood samples will be analysed to measure changes in nitrite concentrations during the intervention. Samples will also be analysed to assess for biomarkers of cardiovascular risk (C reactive protein, glycated haemoglobin, nitro-tyrosine) and direct brain measures such as plasma brain-derived neurotrophic factor (BDNF), plasma amyloid β42 and amyloid β40. A capillary blood sample will be taken and analysed for the concentration of glucose in the blood using a portable glucometer. Dried blood spot samples will be analysed to measure changes in nitrate concentrations during the intervention. Blood spots will be first processed using a standardised elution protocol to obtain a liquid solution of the samples and then analysed for nitrate concentrations using ozone-based chemiluminescence, which is the reference method for the analysis on nitrate in biological fluids. All blood sampling assessment methods will be conducted at baseline and end of study visits. Venous blood samples will be performed by a qualified medical attendant or staff nurse practising at KK Segamat and dried blood spot samples will be collected by a trained data collector.

##### Twenty-four hour urine and spot urine sampling

Both 24-hour urine and spot urine samples will be collected. Twenty-four-hour urine collection has been associated with a having high respondent burden owing to the time consuming nature of this method, particularly in a community and LMIC setting, where 24-hour urine sampling may be logistically difficult. Spot urine sampling is potentially a more convenient and affordable alternative. However, there are still a number of questions about the reliability of spot urine collection as a means of monitoring intervention adherence. Therefore, by using these two methods of urine collection, the authors hope to explore the feasibility of implementing these collection methods within the target population.^42^

Eligible participants will be provided with a kit to collect a 24-hour urine sample during their baseline home visit (part 1). This will be provided 2 days before their clinic visit (part 2). The kit includes: (1) a participant information booklet with written instructions on how to collect the sample; (2) a ‘24-hour urine collection record’ to note essential information about the urine collection; (3) urine-collecting equipment: (a) 2.5-litre screw-capped plastic container for storing the 24-hour urine sample, (b) 1-litre plastic jug which the urine will be voided into, (c) 1-litre screw-capped plastic container either as backup container when the 2.5-litre storage container is full, or for temporal collections of urine made outside the home and (4) a permanent marker pen to note the start and finish times of urine collection in the 2.5-litre container. Trained data collectors will verbally explain the method of 24-hour urine collection to participants. The 24-hour urine collection will be initiated 1 day before their clinic visit and end in the morning of their appointment. Participants will also collect a spot urine sample on the morning of their clinic visit. They will be provided with a 60 mL screw-capped plastic bottle for the spot urine collection. Participants will be instructed by a trained data collector to provide a spot urine sample using the midstream clean-catch technique.

The 24-hour urine samples collected will be assessed for completeness using assessment of the duration of urine collection, the total urine volume and 24-hour urinary creatinine excretion. The urine samples will be excluded from analysis if the time of the collection falls outside the range of 22–26 hours, if the total 24-hour urine volume is less than 500 mL or greater than 6000 mL and if 24-hour creatinine excretion is less than 3 mmol or greater than 25 mmol in women, or less than 6 mmol or greater than 30 mmol in men. Urinary sodium will be determined using the ion‐selective electrode method. For nitrate, samples will be diluted 1:100 and then analysed for nitrate concentrations using ozone-based chemiluminescence, which is the reference method for the analysis on nitrate in biological fluids.

##### Saliva sampling

Whole saliva will be collected using the passive drool technique. One millilitre of which will be collected into one collection tube. Participants will be asked to generate some saliva in their mouth and when ready, the participant should hold the adaptor with collection tube attached to their mouth and pass saliva into the tube. This process is repeated until desired amount is collected. To measure nitrate, samples will be diluted 1:100 and then analysed for nitrate concentrations using ozone-based chemiluminescence. For the salivary strips, a dedicated app freely available to download on mobile devices will be used to provide a quantitative reading of the salivary nitrite concentrations as a surrogate marker of dietary nitrate intake.

### Patient and public involvement—post intervention qualitative evaluation

Participants will be invited to provide feedback on their participation in the intervention study via focus groups discussions. The focus group topic guide will also be piloted among a random sample of participants prior to implementation to allow feedback, refinement and tailoring prior to implementation. Two focus group discussions will be conducted within each arm of trial (total 8). Purposive sampling will be used to capture broad variation in age, ethnicity, house location and for better understanding of the phenomenon being studied. All focus groups discussions will be audio recorded and the topics covered will include: (1) access to the food items—financial (affordability), physical factors; (2) cultural acceptability of the recommended food items; (3) family support to adhere to the dietary changes; (4) adherence to the instructions—facilitators and barriers, methods to self-monitor; (5) perceived benefit and side effects of intervention; (6) study context—education material, frequency of visit, location of visits, data collection methods and tools; (7) provision of biomedical samples—barriers, cultural acceptability, difficulty; (8) likes and dislikes in relation to the new dietary options and (9) preferred intervention arm. Finally, a behaviour change theoretical framework will be used to guide the qualitative analysis.^43 44^ This will allow the feedback and recommendations from participants to directly inform refinements and tailoring of the intervention for a follow-on efficacy trial as well as to understand the barriers and facilitators to dietary change among this target group.

### Sample size

A formal sample size calculation has not been performed considering the pilot, feasibility nature of the study. A sample size of 30 per group was based on the estimated effect size provided by the guidelines by Whitehead *et al*,^45^ which outlines the sample size calculation for pilot studies with the aim to maximise resources and avoid occurrence of a type II error. Specifically, a sample size of greater than 25 individuals per group would provide in a 90% powered main trial the ability to detect a small effect size between 0.1 and 0.3. More than 100 participants are expected to complete the trial; that is, an anticipated drop-out rate ≤20%.

### Statistical analysis

As the main aims of this feasibility study relate to the feasibility, acceptability and the potential to deliver a dietary intervention, these data will be reported narratively illustrated with descriptive statistics. The CONSORT 2010 statement will be used to guide the reporting of this information.^36^ Secondary aims are largely descriptive, aiming to provide bounds for key parameters to inform the main trial. Intention-to-treat analysis will be used to include all randomised participants and determine the key outcome measures. The recruitment and retention rate in each arm will be described. It is unlikely that statistically significant differences in retention rates will be discovered, but upper and lower bounds will be estimated and reasons for groups with apparently low recruitment or retention rates will be explored qualitatively. Normality of the distribution of the variables and appropriate transformations (LogX, 1/X, Xn) will be performed if necessary. Summary data will be expressed as mean (SD) or frequency (%). General linear models for repeated measures will be used to detect significant differences between the intervention groups with and without adjustment for baseline levels. χ^2^ test will be used for categorical variables. An interaction term (time×group) will be built to assess between-group interactions in changes in the measured outcomes during the interventions. Dietary data will be analysed using the Nutritionist Pro Software (V.7.5).

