## Methods and analysis

### Study design

The DePEC-Nutrition feasibility study is a 6-month randomised 2×2 factorial trial including four parallel arms: (1) control, (2) high-nitrate vegetable consumption, (3) low salt consumption and (4) combined high-nitrate vegetable consumption plus low salt consumption. The trial will be conducted among 120 middle-aged and older Malaysian adults. Sponsor and grant number: GHR Group: 16/137/62—NIHR Global Health Research Group on DePEC, Newcastle University, UK. The Standard Protocol Items: Recommendations for Interventional Trials reporting guidelines were used to guide the preparation of this protocol.^31^

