**Figure 1 F1:**
[figure not shown]
A flow diagram providing an overview of the study procedures.

An interim 2-month visit will take place for those in the intervention groups only, to provide reinforcement messages relating to the allocated dietary intervention and with a view to enhancing compliance with the intervention. In addition, a brief adherence questionnaire will be administered, body weight and resting blood pressure will be measured and salivary strip and spot urine samples will be collected. The same measurements and further dietary reinforcement messages will be conducted at an interim 4-month visit for the participants allocated to the intervention arms. Participants in the control arm will only have one interim visit at month 4 and will have their weight and blood pressure measured. The end of study visit (at KK, Segamat) will include the conduction of the measurements collected at baseline, including cognitive assessment, dietary assessment and collection of biological samples (blood, dried blood spots, 24-hour urine and spot urine samples, saliva samples, salivary strips). In addition, an exit group session (focus group evaluation) and a self-administered feedback questionnaire will be scheduled to evaluate the adherence to the interventions and obtain detailed feedback on the overall study protocol. Finally, the participants will be offered a token of appreciation to acknowledge their participation in the study and to compensate for travel expenses. This is usually to the value of RM 25.

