### Outcome measures

Outcome assessments will be conducted at baseline, month 4 and month 6 for all groups, with an additional assessment visit at month 2 for those in the intervention groups. Assessments at baseline and month 6 will be conducted in clinic/at home, with remaining assessments completed in the participants own home. The same instruments will be used for measurements at each time point. Assessors are trained prior to the assessments to follow a standardised protocol. A timeline of the study procedures can be found in table 1.

**Table 1 T1:** Timeline of study procedures

Procedures	Consent/screening	Baseline Week 1	Week 2	Week 4	Week 6	Week 8	Week 10	Week 12	Week 16	Week 18	Week 20	Week 22	End of study Week 24
Inclusion/exclusion	✓												
Consent	✓												
Activities for intervention group													
Dietary education		✓											
Reinforcement at home visit		✓				✓			✓				
Group education counselling session		✓											
Home visit						✓			✓				
SMS messages			✓	✓	✓	✓	✓	✓	✓	✓	✓	✓	✓
Activities for control group													
General health promotion message		✓											
Home visit									✓				
Study measurements													
Sociodemographic		✓											
Concomitant medication check list		✓				✓							✓
Any medical events		✓				✓							✓
Physical activity (IPAQ)		✓											✓
Depression (GDS)		✓											✓
Food Frequency Questionnaire (FFQ)		✓											✓
24-hour dietary recall		✓											✓
Nitrate: urine		✓*				✓†‡			✓‡				✓*
Salt: urine		✓*				✓†‡			✓‡				✓*
Cognitive performance		✓											✓
Resting blood pressure		✓				✓†			✓				✓
Body composition		✓				✓†§			✓§				✓
Physical function		✓											✓
Blood sample and dried blood spot		✓											✓
Saliva sample and salivary strips		✓	✓†¶	✓¶	✓

*Twenty-four hour urine and spot urine samples.

†Intervention groups only.

‡Spot urine sample only.

§Body weight only.

¶Saliva strips only.

FFQ, Food Frequency Questionnaire; GDS, Geriatric Depression Scale; IPAQ, International Physical Activity Questionnaire.

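### The plan promises an analysis of all randomised participants but names a repeated-measures model that, as ordinarily run, keeps only completers

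*Protocol article*

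**What the plan says.** The Statistical analysis section fixes both an analysis population and a model. The population: "Intention-to-treat analysis will be used to include all randomised participants and determine the key outcome measures". The model: "General linear models for repeated measures will be used to detect significant differences between the intervention groups with and without adjustment for baseline levels". It adds: "An interaction term (time×group) will be built to assess between-group interactions in changes in the measured outcomes during the interventions". The section does not mention imputation or an all-available-data method, and it does not say which visits enter the model or which of the two estimates, adjusted or unadjusted, is to be reported.

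The Study design section gives the total: "The trial will be conducted among 120 middle-aged and older Malaysian adults". The Sample size section gives 30 per group, expects more than 100 completers, and equates this with drop-out of at most 20%.

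On visits, the Outcome measures section sets baseline, month 4 and month 6 for every arm, "with an additional assessment visit at month 2 for those in the intervention groups". The Study procedure section agrees: "Participants in the control arm will only have one interim visit at month 4". Blood pressure and weight are taken at every assessment visit. Cognition, body composition and physical function are taken only at baseline and the end of the study.

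**The concern.** The conventional general linear model for repeated measures works on one complete outcome vector per participant, and someone missing any modelled value is deleted. With drop-out expected, such a model does not deliver the population promised in the same section. The article would describe as intention to treat what is in practice an analysis of completers.

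The comparison is labelled exploratory, but its output has a stated use. The strengths and limitations list, the Purpose and aims section and the Discussion all say that the results or effect sizes will inform the design and sample size of the follow-on efficacy trial. Estimates from completers are open to bias if drop-out relates to outcome, and they discard interim values from people who left late.

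There is also a structural gap. Control has no month-2 blood pressure or weight, so a time-by-group model needs a stated set of visits. Finally, two estimates are planned and neither is designated, although they differ in precision.

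**Working it through.** **The plan's own figure.** At 20% drop-out, completers = 120 × (1 − 0.20) = 96, so 24 are lost. This does not match more than 100 completers, which needs drop-out below 1 − 100/120 = 16.7%, that is, fewer than 20 lost. The two statements disagree at the limit, so both are carried forward.

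**Participants kept under listwise deletion.** Inputs: 30 per arm (Sample size section), 20% drop-out before month 6 spread evenly over arms (assumed), no other missed visits. Each arm with complete scheduling keeps 30 × 0.80 = 24.

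| Visits modelled | Outcomes | Control | Each intervention arm | Total |
|---|---|---|---|---|
| 0, 6 | cognition, body composition, physical function | 24 | 24 | 96 |
| 0, 4, 6 | blood pressure, weight | 24 | 24 | 96 |
| 0, 2, 4, 6 | blood pressure, weight | 0 | 24 | 72 |

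At 16.7% drop-out the totals are 100, 100 and 75. If 5% to 10% of the remaining participants also miss month 4 (an assumption), the 0, 4, 6 model keeps 96 × 0.95 = 91 to 96 × 0.90 = 86. The 0, 6 outcomes lose nothing from a missed interim visit.

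**What a likelihood-based fit keeps.** A random-intercept mixed model was fitted to simulated data with 30 per arm, no control value at month 2, and month 6 missing for 6 of 30 in each arm. All 120 participants contributed, and 15 of the 16 arm-by-visit means were estimable. The exception is control at month 2, which no model can supply from these data.

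**Adjusted against unadjusted.** For an outcome measured twice, the unadjusted time-by-group term is a comparison of change scores. With equal variances and baseline to follow-up correlation r, the ratio of the ANCOVA variance to the change-score variance is (1 − r²) / (2(1 − r)) = (1 + r)/2. The article gives no r. At assumed values of 0.5, 0.6 and 0.7 the ratio is 0.75, 0.80 and 0.85, so adjustment lowers the variance by 15% to 25%.

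**The case against.** The strongest reply is that the article never mentions listwise deletion. Its wording does not exclude a likelihood or generalised least squares fit, or imputation set out in an analysis plan that is not shown. That stands as far as it goes: a reader might infer that the named model cannot give an intention-to-treat analysis, and the documents do not support a word that strong. What remains is that the article states both a population and a model, that the usual form of the model does not deliver the population, and that nothing in the text reconciles them.

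A reader might also infer that the whole control arm would vanish from the blood pressure analysis. That needs a between-arm model including month 2, which the article does not state. Its common schedule is baseline, month 4 and month 6, and month 2 is described as additional and serves reinforcement and compliance. The 0 of 30 in the table shows why the visits should be named; it is not a description of what is planned.

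A third inference is a definite bias in the effect estimate. With an assumed SD of 14 mm Hg, correlation of 0.6, true effect of −4 mm Hg and about 15% drop-out driven by poor response in the active arm only, a simulated completers' estimate is about −4.7. With the same drop-out mechanism in both arms it is −4.0, which is no bias. Nothing in the article supports the one-sided mechanism. The 0.7 mm Hg shift is also small beside the standard error at 24 per arm: 14 × √(1 − 0.6²) × √(2/24) = 3.2 with adjustment, and 14 × √(2 × 0.4) × √(2/24) = 3.6 for change scores.

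Lastly, adjustment is already planned, and the comparison is exploratory. Both are true. They lower the weight of the point about designating one estimate without removing it.

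**Conclusion.** The point holds at moderate severity. The stated population and the model as ordinarily run do not match. Up to 24 of 120 participants (20%) would be left out at the drop-out ceiling, or fewer than 20 if more than 100 complete. This assumes the conventional complete-vector form of the model and no imputation. Month 2 cannot enter a comparison with control for blood pressure or weight, whatever the model. Reporting the adjusted estimate gains 15% to 25% in variance over the change score if r lies between 0.5 and 0.7, a range assumed here.

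The consequence is confined to the secondary effect estimates and their use in planning the next trial. The primary outcomes are feasibility measures reported descriptively and do not depend on this model. The size and direction of any bias from drop-out cannot be known from the documents.

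**What to change.** 1. For blood pressure and weight, replace the named model with a likelihood-based linear mixed model (REML, unstructured covariance) on all available data. Take baseline as a response with its mean constrained equal across arms. If baseline is used as a covariate instead, state that participants with no post-baseline value do not contribute.
2. State that comparisons with control are made at months 4 and 6 only, and describe month 2 within the three intervention arms.
3. For outcomes measured only at baseline and month 6, report the baseline-adjusted estimate, from ANCOVA or the equivalent constrained model. ANCOVA at month 6 is itself a complete-case analysis, so changing the model does not recover drop-outs here. Say that participants without a month-6 value add no direct information on the effect, and do not describe this analysis as including all randomised participants unless missing values are imputed.
4. Designate the baseline-adjusted estimate as the one reported.
5. Reconcile the two drop-out statements: more than 100 completers of 120 means drop-out below 16.7%, not up to 20%.

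The cost is wording and modest analysis work. No extra visits, measurements or participants are needed.

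### The plan promises to include all randomised participants but names a model that, as usually fitted, analyses completers only: about 96 of 120 at the anticipated upper limit of drop-out

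*Protocol article*

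**What the plan says.** Two statements in the Statistical analysis section of the protocol article bear on this. On the analysis set: "Intention-to-treat analysis will be used to include all randomised participants". On the model: "General linear models for repeated measures will be used to detect significant differences between the intervention groups with and without adjustment for baseline levels". A time-by-group term is added, but the section does not list the visits that form the time factor.

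On numbers, the Study design section says: "The trial will be conducted among 120 middle-aged and older Malaysian adults". The Sample size section gives 30 per group and expects some loss: "More than 100 participants are expected to complete the trial; that is, an anticipated drop-out rate ≤20" per cent.

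The visit schedule differs by arm. The Study procedure section says: "An interim 2-month visit will take place for those in the intervention groups only". Controls have a single interim visit, at month 4. The Outcome measures section sets baseline, month 4 and month 6 for every arm, with month 2 as an extra visit in the intervention arms. Blood pressure and weight are taken at every outcome visit. The cognitive tests and the 24-hour urine collection are done only at baseline and end of study. Collections that fail the limits on duration, volume or creatinine are removed: "The urine samples will be excluded from analysis".

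**The concern.** In its classical form, a general linear model for repeated measures treats each person's visits as one multivariate row. A row with a gap is dropped. With drop-out expected, such a model describes completers, while the text promises everyone randomised. Both statements are in the same section, so this is a disagreement between two things the plan says.

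Two features of the design add to it. Blood pressure and weight have a month-2 value in three arms and none in control, so the choice of time levels decides whether controls stay in the model at all. In addition, the 24-hour urine outcome needs two valid collections per person, so losses to invalid samples come on top of drop-out.

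At stake are the effect estimates for blood pressure and cognition, which the Purpose and aims section and the Discussion intend for sizing the efficacy trial. If those who leave differ in their earlier response from those who stay, a completer estimate can be biased.

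**Working it through.** **Inputs from the protocol article.** 120 randomised in four arms of 30; drop-out of at most 20%; the visit schedules above.

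**The plan's own completer figure.** Completers = N × (1 − d). At d = 0.20: 120 × 0.80 = 96, or 30 × 0.80 = 24 per arm. This does not reproduce the expectation of more than 100, which needs d below 1 − 100/120 = 16.7%. The figure of 24 per arm is also below the more than 25 per group that the Sample size section relies on. Both rates are carried forward.

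**Participants kept when anyone with a gap is dropped.** This assumes equal drop-out in each arm, every drop-out missing month 6, and no other missed visits. Controls kept are in brackets.

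| Visits entered | No drop-out | 16.7% | 20% |
|---|---|---|---|
| Baseline, 2, 4, 6 | 90 (0) | 75 (0) | 72 (0) |
| Baseline, 4, 6 | 120 (30) | 100 (25) | 96 (24) |
| Baseline, 6 | 120 (30) | 100 (25) | 96 (24) |

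The first row is 3 × 30 × (1 − d), because every control lacks month 2 by design. The other rows are 4 × 30 × (1 − d). Cognition falls in the third row, which month 2 does not touch.

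**24-hour urine.** The article gives no rate of valid collections, so 80% to 90% per visit is assumed here. With 20% drop-out and two valid samples needed:
- at 80%: 120 × 0.8 × 0.8² = 61
- at 90%: 120 × 0.8 × 0.9² = 78

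That is about 15 to 19 per arm.

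**Same data, likelihood-based mixed model.** On baseline, month 4 and month 6, with baseline among the outcomes, all 120 participants with a baseline value contribute, including all 30 controls, at 0%, 16.7% and 20% drop-out.

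**Possible bias, as an illustration only.** None of these inputs is in the article: systolic SD 15 mm Hg, between-visit correlations 0.6 to 0.7, true effect −3.0 mm Hg, and 20% leaving after month 4. Leaving is unrelated to response in control and related to poor month-4 change in the active arm. A large-sample simulation gives:

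| Log-odds of leaving per SD of poor change | Completers, change from baseline | Completers, baseline-adjusted |
|---|---|---|
| 0 | −3.0 | −3.0 |
| 0.4 | −3.7 | −3.5 |
| 0.8 | −4.2 | −3.8 |

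An analysis valid under missing at random that uses month 4 returns −3.0 at log-odds 0.8. If good responders leave instead, the shift of 1.2 changes sign: −3.0 + 1.2 = −1.8.

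**Scale.** The standard error of a baseline-adjusted two-arm contrast with 24 per arm is 15 × √(1 − r²) × √(2/24). This is 3.5 mm Hg at r = 0.6 and 3.1 at r = 0.7. A shift of 1.2 is about a third of that.

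**The case against.** The strongest reply is that a journal article condenses the full protocol. How missing values are handled and how a model is estimated are commonly left to the analysis plan, which is not shown. The text does not mention dropping incomplete cases, and it does not exclude imputation or likelihood estimation. This stands in part. The absence of a missing-data rule is not the point, and a reader might infer too much by saying that the intention-to-treat analysis cannot be delivered. The documents support only that this model does not deliver it as usually fitted and without imputation. The mismatch between the named set and the named method remains.

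A reader might also infer that the blood pressure model loses every control. That holds only if month 2 is entered as a time level. The article does not say so, and the Outcome measures section gives a schedule common to all arms on which controls lose drop-outs only.

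A third reply is that the bias example is constructed. This also stands. The article gives no drop-out mechanism, the direction reverses under the opposite one, and the shift is small beside the sampling error.

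Finally, the primary outcomes are feasibility measures reported descriptively, and the article itself calls the comparative analysis exploratory. This limits the severity.

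**Conclusion.** The point holds in a limited form. An analysis said to include all randomised participants is paired with a model that, fitted in the usual way, would analyse about 96 of 120 (24 per arm) at 20% drop-out, or 100 at 16.7%. These counts assume equal drop-out across arms and no imputation. Loss of all controls is conditional on entering month 2 for blood pressure or weight, and does not concern cognition. The urine range of 61 to 78 rests on an assumed validity rate.

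It is tempting to conclude that the trial will overstate its effects. The documents do not support this: bias is possible if leaving depends on earlier response, but its size and direction are unknown. This should be fixed, because the estimates are meant for designing the next trial. It does not threaten the feasibility conclusions.

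**What to change.** In the Statistical analysis section:

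- **Blood pressure and weight.** Replace the named model by a likelihood-based mixed model for repeated measures on the visits common to all arms (baseline, month 4, month 6). Put baseline in the outcome vector with baseline means constrained equal across arms, use an unstructured covariance, and use all available data. Every randomised participant with a baseline value then contributes. With baseline only as a covariate, anyone leaving before month 4 would still drop out of the analysis. Report month 2 descriptively for the active arms.
- **Outcomes measured only at baseline and month 6 (cognition, 24-hour urine).** Use a baseline-adjusted analysis as randomised, with multiple imputation as a sensitivity analysis. The main analysis here still rests on those with both values, and the text should say so.
- **Intention-to-treat sentence.** Reword to: as randomised, using all available data, with the number analysed per arm for each outcome.

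The cost is a few sentences, different model syntax and slightly more analysis work. No new data are needed.
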